### Exclusion criteria

Healthy participants with any of the following conditions will be excluded: (1) use of a cardiac pacemaker or implanted metal (such as brain metal electrodes [except titanium], cochlear implants, or pulse generators); (2) conditions that may potentiate seizures (such as a history of epilepsy, sleep deprivation, alcohol dependence, or ingestion of olanzapine or lithium carbonate); and (3) pregnancy or lactation.

Patients who meet any of the following conditions will be excluded: (1) patients who have received other treatments that may affect the observations in this study and those who do not follow the study protocol; (2) patients with severe heart, liver, spleen, lung, or kidney disease or mental illness; (3) patients with aphasia, deafness, severe cognitive impairment, or other conditions that hinder their ability to communicate properly; (4) patients unwilling to undergo acupuncture or basic therapy; (5) patients who cannot complete the treatment and may not show good compliance; (6) patients who did not experience physical paralysis after illness; (7) patients who experienced stroke more than three times; (8) patients who received a cardiac pacemaker or other implanted devices such as brain metal electrodes (except titanium), cochlear implants, or pulse generators; (9) patients with conditions that may potentiate seizures, such as a history of epilepsy, sleep deprivation, alcohol dependence, or ingestion of olanzapine or lithium carbonate; and (10) pregnant or lactating patients.

### Randomisation and allocation concealment

A total of 80 healthy participants and 40 patients with post-stroke hemiplegia will be recruited. The 80 healthy participants will be randomised 1:1:1:1 to 2-Hz, 50-Hz, 100-Hz, and sham electroacupuncture groups. The 40 patients with post-stroke hemiplegia will be randomised 1:1 to an opposing needling group or a conventional treatment group. Randomisation will be performed by the Package for Encyclopedia of Medical Statistics 3.1 software (West China School of Public Health, Sichuan, China) and will be overseen by an independent statistician. Healthy participants will be sequentially assigned a random number from 1 to 80, and patients with post-stroke hemiplegia will be sequentially assigned a random number from 1 to 40. Opaque sealed envelopes will be numbered consecutively with a serial number on the outside for randomisation and will contain the allocation information. The envelope will be opened when the participant or patient enters the trial after providing informed consent. Healthy participants will then be allocated to one of the four groups and the patients will be allocated to one of the two groups. All participants and patients will receive an intervention according to their group allocation. The random allocation sequence and the opaque sealed envelopes will be kept by two independent researchers.

### Blinding

Given the nature of the interventions, blinding of the acupuncturists to the trial condition will be difficult. Therefore, in order to maintain blinding, the participants, researchers and the statistician will be blinded by the randomisation procedure. The data will be analysed by two statisticians who will otherwise not be involved in this trial and will remain naive to all study processes.

### Study procedure

The healthy volunteers who consent to participate in the study will complete magnetic resonance imaging (MRI) in Guangdong 999 Brain Hospital, and finish the MMSE, physical examination, and BMI evaluation in an examination room at South China Research Center for Acupuncture and Moxibustion, Medical College of Acu-Moxi and Rehabilitation, Guangzhou University of Chinese Medicine. The patients with post-stroke hemiplegia who consent to participate in the study will undergo MRI, National Institutes of Health Stroke Scale (NIHSS), FMA, Barthel index, and physical examination at a rehabilitation room in Guangdong 999 Brain Hospital. All participants will sit on a treatment chair facing the neuroimaging navigation and TMS machine to enable the location of the correct brain regions.

This study will be divided into the following parts:

Part 1: Effect of different frequencies of electroacupuncture on the excitability of M1 in healthy participants. Firstly, the cortical stimulation will be performed on the left and right M1 of all healthy participants while recording the RMTs and MEPs of bilateral thenar muscles. And then, they will receive 2-Hz, 50-Hz, 100-Hz, or sham electroacupuncture intervention on their left limbs for 20 minutes to explore the optimal frequency. Finally, the RMTs and MEPs both will be tested immediately after intervention within 5 minutes again.

Part 2: Effect of opposing needling on the excitability of M1 in patients with post-stroke hemiplegia. Firstly, the cortical stimulation will be performed on the left and right M1 of patients with post-stroke hemiplegia before the treatments while recording the RMTs and MEPs of bilateral thenar muscles. And then, on the premise of the same conventional treatments and rehabilitation trainings, all the patients will opposing needling as the optimal frequency of electroacupuncture acquired from Part 1 or sham electroacupuncture. After ten opposing needling treatments or ten sham electroacupuncture interventions, the RMTs and MEPs both will be detected again.

Part 3: The physiological and pathological data will be combined to determine the relationship between M1 excitability and stroke rehabilitation, explore the effect of opposing needling on M1 excitability, propose a possible hypothesis for the treatment of post-stroke hemiplegia by opposing needling, and explore the possibility of using M1 excitability to predict stroke recovery.

### Neuroimaging navigation

All participants will undergo MRI (3.0 T) at Guangdong 999 Brain Hospital with an MRI scanner (Signa EXCITE 3.0 T HD, IGE, USA), and an MRI T1 file will be imported into the neuroimaging navigation system (Brainsight® 2.3.3.dmg) to reconstruct a 3-D brain (Fig. 3). Targets with a 4×3 square grid will be built on the M1 region on the 3-D brain (Fig. 4). The neuroimaging navigation system will be used to follow the stimulator coil of the TMS in real time.

**Fig. 3 Fig3:**
[figure not shown]
Three-dimensional (3-D) brain reconstruction

**Fig. 4 Fig4:**
[figure not shown]
Targets with a 4×3 square grid built on the M1 region on the 3-D brain

### Transcranial magnetic stimulation

TMS will be performed by using a figure-eight stimulator coil before and after the intervention. The stimulator coil will be moved over the left and right M1 in order to identify the TMS hotspot [26] among targets based on the 4×3 square grid on the M1 region on the 3-D brain.

### Electromyography (EMG) measurement

RMTs and MEPs induced by TMS will be recorded from bilateral thenar muscles. Surface electrodes will be used to record the RMTs and MEPs of the thenar muscles and placed on the skin over the thenar muscles after skin disinfection. The surface recording electrodes will be placed bilaterally on each side of the thenar muscles, and the reference electrodes will be placed directly next to them (1 cm). Two ground wire disc electrodes will be placed on the upper edge of radius styloid process to reduce interference to the EMG signal. All electrodes will be checked every 15 min to ensure that they are in good contact with the skin and underlying muscles.

### Interventions

#### For healthy participants

Firstly, after skin disinfection, the K Streitberger placebo [27], the validated and reliable single-blind acupuncture needles (Huatuo, Suzhou Medical Supply Factory Co, Ltd, Suzhou, China), will be placed on the skin of Quchi (LI11), Zusanli (ST36), Hegu (LI4), and Chongyang (ST42) of the left limb of all healthy participants separately. Secondly, four sterile acupuncture needles (size 0.30×25 mm and 0.30×40 mm; Huatuo, Suzhou Medical Supply Factory Co., Ltd, Suzhou, China) will be inserted separately through the K Streitberger placebo of the left limb. For healthy participants in electroacupuncture groups, the acupuncture needles will be inserted approximately 15–30 mm into the skin and connected to an acupuncture point nerve stimulator (HANS-200A). The electroacupuncture frequency will be 2 Hz, 50 Hz, and 100 Hz, the intensity will be set to the maximum-tolerated intensity for each participant, and the time will sustain 20 min. Based on the above operation, the participants in electroacupuncture groups feel the Deqi sensation (a sensation of soreness, distention, numbness, or radiating that indicates effective needling). Besides, for healthy participants in the sham electroacupuncture group, the difference is that the acupuncture needles will be placed on the skin through the K Streitberger placebo without inserting into the skin and the K Streitberger placebo will be connected to the same stimulator (HANS-200A) without electricity output. Thus, the participants in the sham electroacupuncture group will not feel the Deqi sensation. All healthy participants will only receive one electroacupuncture or sham electroacupuncture intervention instantaneously.

#### For patients

All patients with post-stroke hemiplegia will receive conventional treatment according to the *Guidelines for the diagnosis and treatment of acute ischemic stroke in China* 2018 [28], which includes active control of blood pressure and blood sugar level, nutritional support, administration of the neurotrophic drug citicoline sodium 0.1~0.2 g, three times a day, orally; and statin treatment if considered necessary by the clinician. The patients will receive the anticoagulant aspirin 0.15~0.30 g, once a day, orally, and patients who cannot tolerate aspirin will receive clopidogrel instead. The patients will also receive basic rehabilitation training, including physical therapy, occupational therapy, and additional training as appropriate, e.g., weight loss support training or isokinetic muscle training. In addition, patients who suffered from the right side of the affected limb due to post-stroke hemiplegia in the opposing needling group will receive electroacupuncture on the left side of the unaffected limb in total 10 times (once per day for 5 consecutive days followed by a 2-day break altogether 2 weeks.) The acupoints and the operation method of electroacupuncture were described as the healthy participants in electroacupuncture groups. The electroacupuncture frequency will be the optimal frequency acquired from the healthy participants in electroacupuncture groups and the intensity will be set to the maximum-tolerated intensity for each patient and the time will sustain 20 min. Besides, the patients in the conventional treatment group will receive sham opposing needling intervention on the left side of the unaffected limb in total 10 times. The course of treatment will be the same as the patients in the opposing needling group. The operation method of sham electroacupuncture was also described as the healthy participants in sham electroacupuncture groups.

To maintain study fidelity, all researchers will receive training on the study methods, techniques, and study monitoring. All research staff will be tested after training to ensure they can consistently replicate the protocol.

### Outcome measures

#### Primary outcome measure

The primary outcome measure will be the per cent change in the RMTs of the thenar muscles at baseline and after the intervention. The RMTs of the thenar muscles will be delivered by a TMS pulse every 30 s bilaterally to the left or right M1, respectively, for 10 pulses in the fully relaxed state. The MEP of the thenar muscles should be greater than or equal to 50 μV for at least half (5/10) of the TMS pulses. The RMT is defined as the minimum intensity that is needed to elicit the MEP ≥ 50 μV in at least 50% of the pulses.

### Secondary outcome measures

The secondary outcome measures will be the amplitude (μV) and latency (ms) of the MEPs of the thenar muscles at baseline and after the intervention. The MEPs will be induced by a single TMS pulse as a proxy for the TMS-evoked potential in this study. In practical terms, the RMTs, which is the minimum intensity of the TMS from each participant, will be detected and recorded first. Then 110% of the RMTs value will be used as the relative stimulation intensity of the TMS, which will be calculated by adding 10 percentage points of the basic RMTs value to detect the excitability of the bilateral M1 every 30 s for three TMS pulses in this study [29].

### Safety and adverse events

To ensure safety and protect the rights of the participants, they will be assessed before and after the treatment and instructed to report any abnormal reactions or uncomfortable sensations to the researchers. Treatment-related adverse events, including bleeding, haematoma, pain, or vegetative symptoms, will be treated and closely monitored by the researchers [30]. However, for serious adverse effects such as hearing impairment or seizures, the trial will be immediately stopped and necessary medical treatments will be applied. These serious adverse events will be recorded and subsequently monitored by the China Clinical Trial Registration Ethics Committee.

### Data collection and management

The demographic information for each participant, including the participant’s age, sex, height, weight, dominant hand, medical history, outcome data, and reason for attrition, will be recorded in the case record form. Data will be labelled by a unique numeric identifier and recorded by the investigator. Upon completion of the trial, the electronic data will be examined twice by two independent data managers, and value pairs will then be compared for discordances, followed by resolution of discordances by referral to the original data. In addition, all participant’s data will be encoded in the ResMan Research Manager, which is a public clinical trial data acquisition and management system that was established by the data monitoring committee of the Chinese Clinical Trial Registry. The China Clinical Trial Registration Ethics Committee will also audit the study randomly as an independent body. The data monitoring committee will be responsible for data monitoring to evaluate safety issues every 6 months and monitor attrition rates; adverse events will be monitored quarterly, but special attention will be given to events requiring medical or surgical intervention that require hospitalisation and/or prevention of death and long-term disability.

The principal investigator, the co-investigators, and the acupuncturists administering the intervention are all experienced acupuncturists who can adroitly handle an acupuncture emergency. To maintain study quality, the researchers, including the acupuncturist and research assistants, will receive specialised training with a test-retest of all trial methods, study techniques, and monitoring methods. The outcome assessment and data analysis study personnel will be blinded to the study procedures. Participation will be terminated upon participant request or withdrawal of consent. Investigators may also exclude participants from the study to ensure their safety.

### Sample size calculation

The sample size for the 2-Hz, 50-Hz, 100-Hz, and sham electroacupuncture groups was 20, which was calculated according to the following statistical formula: n = $$ {\upvarphi}^2\Big(\sum {\mathrm{S}}_{\mathrm{i}}^2/ $$g)/[$$ \sum {\left({\overline{\mathrm{X}}}_{\mathrm{i}}-\overline{\mathrm{X}}\right)}^2/\left(\mathrm{g}-1\right)\Big] $$, where g represents the number of groups and group allocation ratios are equal. Based on the preliminary experiment, the average RMT reductions in each group were expected to be − 4.44, − 3.33, − 1.75, and − 0.91, with standard deviations of 3.69, 2.89, 3.40, and 1.92, respectively. The *P*-value for the two-sided test was 0.05, and the test power was 80%. Thus, using PASS 15 software, the optimal sample size was 72. Considering a 10% dropout rate, a total of at least 80 participants would have to be included, with 20 participants included in each group.

For patients with post-stroke hemiplegia in the opposing needling or conventional treatment groups, the sample size was 20 based on the statistical formula *n* = $$ {\left[\frac{\left({Z}_{\propto }+{Z}_{\beta}\right)\upsigma}{\updelta}\right]}^2 $$. The main primary outcome measure is RMT. *δ* is the RMT of the thenar muscles, and according to our previous trials, the minimum clinically significant RMT value was estimated to be 3.57 [24]. Thus, *δ* was estimated to be 3.57. ∝is the significance level; *β* is the power of the test. In this study, ∝= 0.05, *Z*_∝_= 1.96, *β* = 0.80 (80%), and *Z*_*β*_ = 0.84, while σ was estimated at 3.67. With the PASS 15 software, the optimal sample size of the opposing needling and conventional treatment groups was calculated as 18 cases. Considering an overall dropout rate of 10%, including cases lost to follow-up and patients refusing to follow-up, at least 20 participants would be required in the treatment and control groups. Thus, at least 40 patients with post-stroke hemiplegia would have to be recruited for the study.

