### Statistical analysis

Statistical analysis of the RMTs and MEPs will be performed with Statistical Package for Social Science (SPSS) software for Windows, version 17.0 (SPSS Inc., Chicago, IL, USA). D’Agostino’s test for normally distributed variables and Levene’s test for homogeneity of variance will be applied. For healthy participants, if measurement data are normally distributed, then Bonferroni’s test will be used to analyse between-group differences for each participant pre- and post-electroacupuncture or sham electroacupuncture. Otherwise, Kruskal-Wallis’ H test for a nonparametric distribution will be used. The level of significance is set at 5% for all comparisons. For patients with post-stroke hemiplegia, if the measurement data are normally distributed, then an independent *t* test will be used to analyse between-group differences for each participant pre- and post-electroacupuncture or sham electroacupuncture. Otherwise, the Wilcoxon rank-sum test for a nonparametric distribution will be used. The level of significance will be set at 5% for all comparisons.

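### The stated Part 1 inputs need 60 participants, not 72, for 80% omnibus power; that 80% does not describe most pairwise comparisons; and the printed patient formula lacks a factor of 2, although the patient numbers are right

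*Protocol article*

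**What the plan says.** **Healthy participants (Part 1).** The Sample size calculation section prints a formula for comparing g means: a squared multiplier times the mean group variance, divided by the between-group variance of the means. Its inputs are:

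- Means: "the average RMT reductions in each group were expected to be − 4.44, − 3.33, − 1.75, and − 0.91".
- Spread: "with standard deviations of 3.69, 2.89, 3.40, and 1.92, respectively".
- Allocation: "group allocation ratios are equal".
- Error rates: the "two-sided test was 0.05, and the test power was 80" per cent.
- Result: "the test power was 80%. Thus, using PASS 15 software, the optimal sample size was 72", raised to 80 (20 per group) for 10% dropout.

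**Patients (Part 2).** The same section prints n = [(Z_α + Z_β)σ/δ]², with Z values 1.96 and 0.84, σ = 3.67 and δ = 3.57. It calls β the power and sets it to 0.80. It then reports that "the optimal sample size of the opposing needling and conventional treatment groups was calculated as 18 cases", raised to 20 per group and 40 in total for 10% dropout.

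**Analysis.** For healthy participants with normal data, the Statistical analysis section says "Bonferroni’s test will be used to analyse between-group differences". For non-normal data it names the Kruskal-Wallis H test. Patients are compared with an independent t test, or the rank-sum test if data are not normal.

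**The concern.** A sample-size statement lets the reader recover N from its inputs and tells the reader how much power the planned test has. Here the inputs for the healthy groups lead to a smaller N than the one stated. The calculation also concerns an overall comparison of four groups, whereas the test named for normal data is a pairwise one.

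The second gap matters more. The Objectives section lists finding the optimal frequency as a secondary aim, and the Study procedure and Interventions sections carry that frequency into Part 2. If the stated 80% is taken to cover the comparisons between frequencies, a non-significant difference could be over-read.

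For patients, anyone who puts the stated values into the printed formula gets about half the stated size per arm.

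**Working it through.** **1. Healthy groups: trying to reproduce 72**

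Inputs from the Sample size calculation section: means −4.44, −3.33, −1.75, −0.91; SDs 3.69, 2.89, 3.40, 1.92; g = 4; α = 0.05; power 80%.

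- Mean variance: (13.616 + 8.352 + 11.560 + 3.686)/4 = 9.304, so the root-mean-square SD is 3.05.
- Grand mean: −10.43/4 = −2.6075.
- Sum of squared deviations: 3.358 + 0.522 + 0.735 + 2.882 = 7.497. Divided by g − 1 = 3, this is 2.499.
- Ratio in the printed formula: 9.304/2.499 = 3.723.

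The multiplier depends on the error degrees of freedom, so I solved it through the noncentral F distribution, with noncentrality λ = n × 7.497/9.304 and 3 and 4n − 4 degrees of freedom.

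| n per group | Total | λ | Power |
|---|---|---|---|
| 14 | 56 | 11.28 | 78.2% |
| 15 | 60 | 12.09 | 81.4% |
| 18 | 72 | 14.50 | 88.9% |
| 20 | 80 | 16.12 | 92.3% |

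The stated inputs give 60. Simulation with the unequal SDs at 15 per group gives 81% for ANOVA, 86% for Welch's test and 81% for Kruskal-Wallis, so none of these needs 72.

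Among the variants tried, 72 appears only when an input is changed:

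- a single SD of 3.40: 80.5% power at 18 per group;
- α = 0.025: 82.2%;
- the average SD (11.90/4 = 2.975) with α = 0.05/3: 80.3%;
- a 90% power target with the average SD: 90.5%;
- a 90% power target with the infinite-df multiplier: 2.173² × 3.723 = 17.6, rounded up to 18.

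The document does not show which of these, if any, was used. The dropout step is right: 72/0.9 = 80.

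**2. Power of the pairwise comparisons**

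Assumptions: the means belong to 2 Hz, 50 Hz, 100 Hz and sham in the listed order; pooled SD 3.05; 18 per group; 68 error df. Noncentrality is difference/√(2 × 9.304/18) = difference/1.017. The Bonferroni level is 0.05/6 for all pairs, or 0.05/3 if only the sham contrasts are adjusted.

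| Pair | Difference | Six comparisons | Three vs sham |
|---|---|---|---|
| 2 Hz vs sham | 3.53 | 77% | 84% |
| 2 vs 100 Hz | 2.69 | 48% | – |
| 50 Hz vs sham | 2.42 | 38% | 48% |
| 50 vs 100 Hz | 1.58 | 13% | – |
| 2 vs 50 Hz | 1.11 | 6% | – |
| 100 Hz vs sham | 0.84 | 3% | 6% |

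Sensitivity, six comparisons:

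- With all 20 per group retained, 2 Hz vs sham rises to 83% and the others lie between 4% and 54%.
- With pair-specific SDs at 18 per group, 50 Hz vs sham is 57% instead of 38%, and 2 vs 100 Hz is 32% instead of 48%.

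**3. Patients**

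- Formula as printed: [(1.96 + 0.84) × 3.67/3.57]² = 8.29, so 9.
- With the factor 2 for two independent groups: 2 × 8.29 = 16.57, so 17 per arm (normal approximation).
- Exact two-sample t test: 78.5% power at 17 per arm and 80.9% at 18.
- Dropout: 18/0.9 = 20 per arm, 40 in total.

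The stated 18, 20 and 40 therefore reproduce for the planned t test. Nine per arm would give about 49%. Z = 0.84 belongs to 80% power, for which β is 0.20.

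**The case against.** The strongest reply is that nothing here harms the trial. The Part 1 discrepancy is on the safe side, since 72 is more than the inputs require. The patient size is right, was attributed to PASS and matches the planned test, so the formula and the β label are slips on the page. All of this stands, and it rules out treating the point as a blocking error.

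On the mismatch between tests, one could note that Kruskal-Wallis, named for non-normal data in the same groups, is itself omnibus, and that Bonferroni's test may be shorthand for the step after a one-way ANOVA. This is fair. A reader might infer that the analysis contains no omnibus test at all, and the text does not support that. What remains is that no omnibus test is named for normal data and that the pairwise comparisons named there were not what the calculation sized.

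A reader might also infer that no pair reaches 80%. That depends on six comparisons, a pooled SD and 18 per group, none of which the article fixes for this purpose. The 2 Hz vs sham contrast reaches 84% with three comparisons, or 83% with 20 per group and six. The article also nowhere claims 80% for each pair, and choosing a frequency is a secondary, exploratory objective. The over-reading risk is therefore a foreseeable consequence, not something the plan states.

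**Conclusion.** The point holds in three limited parts.

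- **72 does not follow from the printed inputs.** They give 60 for 80% power (81.4%), and 72 gives about 89%. At least one of SD, α or power differs from what produced 72. The size errs upward, so a reading that Part 1 is too small for its overall comparison would be wrong.
- **The stated 80% describes neither the omnibus test nor most pairwise comparisons.** The omnibus test has more. Under the assumptions shown, 2 Hz vs sham is near 80% (77% to 84%), and the three frequency-vs-frequency comparisons have 6% to 48%. The exact values move with the SDs, the number of comparisons and the retained sample, but these three stay well below 80% in every case shown.
- **The patient formula and the β label are misprinted, while the patient numbers are correct.** A reader who inserts the values and gets 9 might conclude that 18 is wrong. It is not: 18 per arm gives 80.9% for the planned t test.

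No recruitment number has to change. The point should be fixed because the stated power bears on how the frequency comparisons will be read.

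**What to change.** Keep 80 healthy participants and 40 patients, and reword two sections.

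- **Part 1 size.** Check the PASS output. Either state that 72 evaluable participants give about 89% power for the omnibus test under the printed inputs (60 would give 81%), or correct whichever input was actually used.
- **Part 1 analysis.** Name the omnibus test for normal data and say which Bonferroni-adjusted comparisons follow it. Give the power of those comparisons with the SD, number of comparisons and evaluable sample assumed, and note that differences between frequencies are not powered.
- **Part 2 size.** Print n per arm = 2[(Z_{α/2} + Z_β)σ/δ]², with β = 0.20. State that this gives about 17 per arm and that the t test raises it to 18.

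The cost is text only. Some stated powers will look less favourable, but no participants are added.
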